### Statistical plans

All statistical analyses will be performed using SAS software (version 9.4 or later). Analyses will be primarily descriptive in nature and will be conducted using non-missing data only.

Except for safety analyses, all efficacy and exploratory analyses will be performed in the full analysis set (FAS), which includes all patients who meet the inclusion and exclusion criteria, unless otherwise specified. Continuous variables will be summarized using the number of observations, mean, standard deviation, median, first and third quartiles, minimum, and maximum. Categorical variables will be summarized as frequencies and percentages. 95% confidence intervals (CIs) will be reported where appropriate. For time-to-event endpoints, analyses will include the number and proportion of patients experiencing each event, along with the corresponding event rates. Kaplan-Meier methods will be used to estimate and graphically present cumulative incidence for both composite and individual endpoints. Changes in eGFR over time will be evaluated using a mixed-effects model for repeated measures (MMRM) to estimate the eGFR slope over the study period.

Safety analyses will be conducted in the safety analysis set (SAS), which includes all patients who have received at least one potassium-binding therapy. The number and proportion of patients experiencing at least one AE, SAE, or ADR will be summarized. Vital signs at each scheduled assessment, as well as findings from physical examinations, electrocardiograms, and laboratory evaluations, will be summarized using descriptive statistics.

A total of four interim analyses are planned, including one primary analysis. The primary analysis is scheduled to occur 48 weeks after enrollment of the final patient.

In addition, predefined subgroup analyses will be performed for the primary and selected secondary endpoints. Subgroups will be defined based on demographic characteristics, baseline disease features (including baseline eGFR to reflect CKD stage), geographic region, and other clinically relevant factors such as history of heart failure, diabetes mellitus, RAASi use, and hyperkalemia treatment patterns.

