The secondary endpoints include: (1) the proportion of patients with normokalemia (serum potassium 3.5-5.0 mmol/L) at each onsite visit; (2) the proportion of patients achieving RAASi optimization with normokalemia at weeks 12 and 24; (3) the percentage change in urinary albumin-to-creatinine ratio (UACR) from baseline to weeks 48 and 96 among patients receiving RAASi at baseline; (4) the proportion of patients experiencing severe hyperkalemia (serum potassium > 6.5 mmol/L) during the 96-week intervention period; (5) medication possession ratio (MPR) for hyperkalemia therapies, defined as the number of days hyperkalemia medication was used between two onsite visits divided by the total number of days between those visits, assessed at each onsite visit; (6) time to first hyperkalemia recurrence; (7) hospital-level hyperkalemia management status at baseline and at weeks 48 and 96; (8) time to first occurrence of any component of the kidney-specific composite endpoint, defined as sustained eGFR decline ≥ 50%, ESRD, or renal death; (9) eGFR slope over the 96-week follow-up period; (10) time to first occurrence of any component of the heart-specific composite endpoint, including rehospitalization for heart failure (rhHF), worsening heart failure, emergency room visits, or cardiovascular death; (11) time to first occurrence of arrhythmia; (12) frequency of serum potassium testing and number of hyperkalemia episodes during the first 48 weeks of intervention (onsite and remote visits), with hyperkalemia defined as serum potassium > 5.0 mmol/L and multiple measurements within 48 h counted as a single episode; (13) the proportion of patients requiring emergency department visits, emergency dialysis, or hospitalization during the 48-week intervention period; (14) safety and clinical assessments, including adverse events (AEs), serious adverse events (SAEs), adverse drug reactions (ADRs); (15) vital signs; (16) physical examination findings; (17) clinical laboratory parameters; and (18) electrocardiographic assessments.

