j. Additional ECGs may be performed if available as per clinical practice. ECG results obtained within 14 days prior to baseline may be used as screening data

k. Vital signs include body temperature, systolic and diastolic blood pressure, pulse rate, and respiratory rate

l. RAASi treatment patterns include whether therapy was initiated and, if so, detailed data (drug/treatment name, usage and dosage, frequency, start and end dates, any changes or interruptions, and reasons for discontinuation, if applicable)

m. Hyperkalemia treatment: Pharmacological treatment includes whether therapy was administered and, if so, treatment name, usage and dosage, frequency, start and end dates, and any changes or interruptions with reasons (if applicable). Non-pharmacological treatment includes treatment name, start and end dates, and reason for change or interruption (if applicable)

n. Concomitant medications will be collected throughout the study. Blood pressure and RAASi treatment in the 3 months prior to enrollment will also be recorded. For patients continuing RAASi treatment during screening, the date of the last dose prior to enrollment should be documented

o. Clinical progression/medical events include: Kidney-specific composite events: sustained eGFR decline ≥ 50%, ESRD, or renal-related death. Cardiovascular-specific composite events: rhHF, worsening HF, emergency room visit, or cardiovascular death. Other events: arrhythmia, hospitalization, emergency dialysis, emergency department visit, and death due to other causes

p. Adverse events (AEs): All AEs and SAEs related to potassium binders, as well as special situations (e.g., medication error, drug abuse, misuse, and pregnancy) involving LOKELMA^®^, will be actively collected. The collection period spans from the time of ICF signing (for patients using a potassium binder prior to enrollment) or the date of treatment initiation (for those starting after enrollment) until 24 h post-discontinuation. AEs involving other products for which AstraZeneca is not the marketing authorization holder (MAH) will be reported spontaneously to the respective MAHs

* Demographic and medical history data collected during the screening period may be used as baseline data

**Table 2 Tab2:** Schedule of activities for sites

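### Kaplan-Meier is planned for the cumulative incidence of secondary endpoints that leave out some or all deaths, so their absolute risks will be overstated once competing deaths occur

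*Protocol article*

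**What the plan says.** The Statistical plans section of the protocol article names both the quantity and the estimator: "Kaplan-Meier methods will be used to estimate and graphically present cumulative incidence for both composite and individual endpoints". The sentence before it adds simpler summaries: "For time-to-event endpoints, analyses will include the number and proportion of patients experiencing each event, along with the corresponding event rates". No competing-risk method is named, and nothing is said about how a death outside an endpoint is handled.

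The Endpoints section lists four time-to-event secondary endpoints:

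- (6) "time to first hyperkalemia recurrence", which includes no death.
- (8) the "kidney-specific composite endpoint, defined as sustained eGFR decline ≥ 50%, ESRD, or renal death", which includes renal death only.
- (10) the heart composite, made up of "rehospitalization for heart failure (rhHF), worsening heart failure, emergency room visits, or cardiovascular death", which includes cardiovascular death only.
- (11) "time to first occurrence of arrhythmia", which includes no death.

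Under Timeline of the study, death counts as completing the study, on the same footing as reaching week 96. Footnote o to Table 1 lists "death due to other causes" among the events collected, outside both composites. The Assessment and data collection section repeats this.

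**The concern.** Cumulative incidence by week 96 is the proportion of patients who actually have the event by then. A patient who dies first of an excluded cause never will. Kaplan-Meier handles that patient as censored, which lets the patients still under observation stand in for the one who died. The result is the risk in a hypothetical population where the competing deaths do not happen. That is a different quantity from the one the plan names.

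The study is single-arm and descriptive, so these absolute risks are read at face value, and no between-arm contrast exists in which the error could partly cancel. Some competing deaths are to be expected: eligibility extends down to an eGFR just above 10 mL/min/1.73 m², follow-up lasts 96 weeks, and the Background itself links raised potassium to mortality in CKD. Subgroups by baseline eGFR and heart failure history are planned for selected secondary endpoints. If these endpoints are among those selected, the overstatement would be larger where mortality is higher and would distort the comparison between subgroups.

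**Working it through.** **The plan's own figure.** The plan gives no expected rate for any time-to-event endpoint. Its only computed figure is the 3.4% precision of the primary endpoint. With 1,000 × (1 − 0.20) = 800 evaluable patients, 1.96 × √(0.45 × 0.55 / 800) = 3.447%, which agrees. Nothing below depends on it.

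**Which deaths compete.**

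| Endpoint | Deaths counted | Competing deaths |
|---|---|---|
| Kidney composite | renal | all non-renal |
| Heart composite | cardiovascular | all non-cardiovascular |
| Arrhythmia | none | all |
| Hyperkalemia recurrence | none | all |
| Non-fatal components (e.g. ESRD, worsening heart failure) | none | all |

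**Direction.** At each event time, the Aalen-Johansen estimator adds (probability of being alive and event-free just before) × (events / number at risk). One minus Kaplan-Meier uses the same fraction, but its multiplier falls only with events of interest and not with competing deaths. That multiplier is never smaller. It is strictly larger once a competing death has occurred, so every later event is over-weighted.

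**Size, with assumed rates.** Let K be one minus Kaplan-Meier at 96 weeks and D the competing-death risk over 96 weeks, each taken alone, with constant hazards. Put a = −ln(1 − K) and b = −ln(1 − D). Then

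incidence = a/(a + b) × [1 − exp(−(a + b))], where exp(−(a + b)) = (1 − K)(1 − D).

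For K = 20%, a = 0.2231:

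| D | b | a/(a + b) | 1 − (1 − K)(1 − D) | Incidence | Excess (points) |
|---|---|---|---|---|---|
| 5% | 0.0513 | 0.813 | 0.24 | 19.5% | 0.5 |
| 10% | 0.1054 | 0.679 | 0.28 | 19.0% | 1.0 |
| 15% | 0.1625 | 0.579 | 0.32 | 18.5% | 1.5 |
| 20% | 0.2231 | 0.500 | 0.36 | 18.0% | 2.0 |

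The relative overstatement runs from about 2% (20/19.5) to 11% (20/18.0).

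For K = 50%, a = 0.6931:

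- D = 10%: 0.868 × 0.55 = 47.7%, an excess of 2.3 points.
- D = 20%: 0.756 × 0.60 = 45.4%, an excess of 4.6 points.

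**Wider range.** Annual competing mortality was varied from 2% to 15% (3.7% to 25.9% over 96/52 = 1.846 years) and K from 5% to 80%. One minus Kaplan-Meier was too high in all 24 combinations, by 0.09 to 8.20 points. One case (K = 20%, 5% a year) was simulated with 400,000 patients and gave 19.15%, against 19.12% by formula.

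**The case against.** The strongest reply concerns size. At K = 20% the excess is 0.5 to 2.0 points. The 95% half-width for a 20% proportion is 1.96 × √(0.2 × 0.8 / n), about 2.5 points with 1,000 patients and 2.8 with 800, so the bias stays inside sampling error. Of the cases worked at 20% and 50%, only 50% incidence with 20% competing death gives an excess (4.6 points) above its half-width (about 3.1 to 3.5). If events come early, fewer deaths precede them and the gap shrinks. All this stands as a limit on the size. It does not justify the estimator, because the error has a known direction and does not shrink with more patients.

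A second reply is that the article condenses a fuller plan that is not shown, and never says in words that deaths are censored. That plan may add a competing-risk analysis. But the article did not leave the estimator open. It named Kaplan-Meier for cumulative incidence on endpoints that death can pre-empt, and censoring is what that method does with such deaths.

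A reader might infer more than the documents support:

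- *That these curves are the only result for the endpoints.* Counts, proportions and event rates are planned too. A rate per person-time at risk, if that is meant, is not inflated by competing death. With 20% dropout anticipated, though, the crude proportion does not replace a correct cumulative incidence.
- *That component curves adding to more than the composite would show the bias.* Components are not mutually exclusive. A patient can have a 50% eGFR decline and later ESRD, so the sum can exceed the composite under any estimator.
- *That starting dialysis should compete with hyperkalemia recurrence.* Nothing in the documents makes recurrence impossible, or ends follow-up, after dialysis.
- *That Kaplan-Meier should be reserved for all-cause death.* All-cause death is not a listed endpoint.

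**Conclusion.** The point holds for the secondary time-to-event endpoints. The estimator named does not match the quantity named, and the mismatch can only overstate absolute risk. That rests on the endpoint definitions and on censoring of excluded deaths, which follows from the method although the article does not spell it out.

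The size is not known. It rests on assumed rates and constant hazards: 0.5 to 2.0 points at a Kaplan-Meier value of 20% with 5% to 20% competing death, less where mortality is low, and several points where events are frequent and mortality high. The primary endpoint, the sample size and the 3.4% precision are untouched, and no test depends on these curves. It should be corrected before absolute risks are reported, but it does not threaten the main result.

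**What to change.** In Statistical plans, replace Kaplan-Meier with the Aalen-Johansen cumulative incidence function for the time-to-event endpoints and their components. State the competing event for each: non-renal death for the kidney composite, non-cardiovascular death for the heart composite, and death from any cause for arrhythmia, hyperkalemia recurrence and the non-fatal components. For a cause-specific death reported as a component, deaths from other causes compete. Label any Kaplan-Meier curve that is kept as a net, cause-specific estimate, not as cumulative incidence.

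The cost is a changed procedure option in the SAS software already planned, plus a sentence or two of text. Death from other causes is already collected, so no new assessment is needed. The article does not say that the date of such a death is recorded, so the sponsor should confirm that the case report form holds date and cause.

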### Timeline of the study

The schedules of study activities for patients and participating sites are summarized in Tables 1 and 2, respectively. Patient enrollment will commence only after completion of comprehensive guideline-directed medical therapy training for HCPs at both the study-wide and individual site levels. The screening period will extend from 14 days to 1 day prior to enrollment. Following enrollment, patients will receive individualized treatment plans and hyperkalemia management strategies determined by their HCPs, including disease education, self-management materials, prescriptions for RAASi, serum potassium monitoring, and potassium-lowering therapies as appropriate. The maximum duration of follow-up will be 96 weeks. After the baseline visit and initial data collection, each participant will attend six scheduled onsite visits at weeks 12, 24, 36, 48, 72, and 96 post-enrollment. Patients who discontinue participation prematurely will be invited to complete an early withdrawal visit. During intervals without scheduled onsite visits, participants will undergo remote follow-up every 4 weeks. Patients will be considered to have completed the study upon completion of the 96-week follow-up, death, or study termination. The study end date is defined as the date of the final visit of the last enrolled patient.

**Table 1 Tab1:** Schedule of activities for patients

Procedure	Screening period	Management period/follow up^a^							Early Withdrawal + 14 day^c^
Visit ^b^	Day − 14 ~ Day-1	Day 0 Baseline *	Week 12 ± 14 days	Week 24 ± 14 days	Week 36 ± 14 day	Week 48 ± 14 days	Week 72 ± 28 days	Week 96 ± 28 days	
	/	V0	V1	V2	V3	V4	V5	V6	
Informed consent	X								
Inclusion and exclusion criteria	X	X							
Demographics ^d^	X								
Medical history ^e^	X								
Physical examination ^f^	X		X	X	X	X	X	X	
Height, weight	X	X	X (weight only, if available as per clinical practice)						
Laboratory tests (Hematology, Clinical Chemistry, Urinalysis)	X^g^		X	X	X	X	X^h^	X^h^	X^i^
12-lead ECG ^j^	X	X	X	X	X	X	X	X	X
Vital signs ^k^	X	X	X	X	X	X	X	X	
Patient’s daily checklist release and/or retrieve		X	X	X	X	X	X	X	X
RAASi treatment pattern ^l^		X	X	X	X	X	X	X	X
Hyperkalemia treatment pattern ^m^		X	X	X	X	X	X	X	X
Concomitant medication ^n^	X	X	X	X	X	X	X	X	X
Clinical progression/medical events collection			X						X
Administration of study intervention		X	X •Patient education at each onsite visit •Patient self-learning						
AE/SAE^p^	X								X

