**Fig. 2 Fig2:**
[figure not shown]
Guideline-directed management algorithm for hyperkalemia in chronic kidney disease

**Table 4 Tab4:** Actions to manage hyperkalemia in chronic kidney disease

1st line: Correctable factors	• Review non-RAASi medications (e.g., NSAIDs, trimethoprim) • Assess dietary potassium intake (dietary referral) and consider appropriate moderation of dietary potassium intake
2nd line: Medications	Consider: • Appropriate use of diuretics • Optimize serum bicarbonate levels • Licensed potassium exchange agents
3rd line: Last resort	• Reduce dose or discontinue RASi/MRA (Discontinuation is associated with increased cardiovascular events. Review and restart RASi or MRA later if the patient’s condition allows.)

RAASi, renin-angiotensin-aldosterone system inhibitor; NASID, nonsteroidal anti-inflammatory drug; RASi, renin-angiotensin system inhibitor; MRA, mineralocorticoid receptor antagonist

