### Assessment and data collection

Demographic data will include age, sex, race, and ethnicity. Medical history will capture comorbid conditions and clinically relevant diagnoses requiring pharmacological treatment within 1 year prior to enrollment. Laboratory assessments will include serum potassium, UACR, and eGFR, with UACR calculated from measured urinary albumin and creatinine concentrations.

Patterns of RAASi use will be documented, including whether therapy was initiated or continued and, where applicable, the specific drug name, dosage, frequency, start and end dates, and any dose modifications or interruptions, together with the underlying reasons. Pharmacological treatments for hyperkalemia will be recorded in a similar manner, including treatment details and reasons for discontinuation or interruption. Non-pharmacological hyperkalemia management strategies will also be documented, including the intervention type, start and end dates, and reasons for any changes or discontinuation. Clinical progression and medical events will include kidney-specific composite outcomes (sustained eGFR decline ≥ 50%, ESRD, or renal-related death), cardiovascular-specific composite outcomes (rhHF, heart failure-related emergency visits, or cardiovascular death), as well as arrhythmias, hospitalizations, emergency dialysis visits, and death from other causes. In addition, the hyperkalemia management status of each participating site will be assessed using a site-level questionnaire administered at baseline and at weeks 48 and 96 following enrollment of the first patient (Table 2).

Safety will be monitored throughout the study period. A comprehensive baseline assessment will be conducted for each participant, including demographic characteristics, medical history, electrocardiograms, laboratory parameters, vital signs, height, weight, and physical examination findings. During the study, vital signs, electrocardiograms, and laboratory assessments will be performed according to the schedule specified in Table 1. AEs, SAEs, and concomitant medication use will be continuously monitored and systematically recorded. Each reported SAE will be individually reviewed to assess its potential impact on participant safety and the overall conduct of the study. Cumulative AEs will be tracked throughout the study, and all AEs will be followed until resolution, stabilization, or completion of the end-of-study visit.

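### The formal safety summaries leave out patients who never receive a potassium binder, and Table 1 footnote p and the main text disagree on which adverse events are recorded and when

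*Protocol article*

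**What the plan says.** Statistical plans in the protocol article takes safety analyses out of the full analysis set (FAS) rule and gives them their own population: "Safety analyses will be conducted in the safety analysis set (SAS), which includes all patients who have received at least one potassium-binding therapy". The next sentence says: "The number and proportion of patients experiencing at least one AE, SAE, or ADR will be summarized". The same paragraph then plans descriptive summaries of vital signs, physical examination, ECG and laboratory data.

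Binder use is not required. Under Timeline of the study, patients receive individualised plans that include "serum potassium monitoring, and potassium-lowering therapies as appropriate". In Table 4, "Licensed potassium exchange agents" is one of three second-line items to consider, beside diuretics and bicarbonate. Targeted RAASi dosing, by contrast, is a core part of the pathway (Intervention) and does not depend on a binder.

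On collection, Table 1 footnote p covers "All AEs and SAEs related to potassium binders, as well as special situations", the special situations being those involving one named product. The window opens at consent for patients already on a binder; for the others it is "the date of treatment initiation (for those starting after enrollment) until 24 h post-discontinuation". Assessment and data collection says instead: "AEs, SAEs, and concomitant medication use will be continuously monitored and systematically recorded".

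**The concern.** A safety population should match the intervention whose safety is being described. Here the intervention is a programme that encourages RAASi continuation and optimization across the cohort, but entry to the safety set depends on one optional component. For patients who start a binder during follow-up, entry also depends on a treatment decision made after enrollment. A patient first given a binder late in follow-up is in the set, and the visit-by-visit summaries may then include visits before exposure. A patient managed throughout with diet or diuretics is not in it, although the same assessments were scheduled and done.

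Two things are at stake. The laboratory, ECG and vital-sign tables would describe a subgroup selected by treatment course rather than the programme's population. And sites have two statements on AE recording that they cannot both follow. The second matters more for timing, because a table can be rerun later but an event that was never recorded cannot be recovered.

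**Working it through.** **The plan's own figure.** The only design figure is the 3.4% precision in Sample size estimation. With p = 0.45 and n = 1,000 × (1 − 0.20) = 800, the half-width is 1.96 × √(0.45 × 0.55 / 800) = 0.0345, which agrees with the stated figure. Nothing in this point changes it; the point concerns population and data scope.

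**Step 1: who is in which analysis.**

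| Item | Source | Patients without a binder included? |
|---|---|---|
| AE, SAE, ADR counts | Statistical plans, safety paragraph | No |
| Vital signs, physical examination, ECG, laboratory summaries | Same paragraph | No |
| Severe hyperkalemia (> 6.5 mmol/L), recurrence, episodes | Endpoints; FAS by default | Yes |
| Kidney and heart composites, eGFR slope, arrhythmia | Endpoints; FAS by default | Yes |
| Emergency visit, emergency dialysis, hospitalization to week 48 | Endpoints; FAS by default | Yes |

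Table 1 schedules ECG, vital signs, physical examination and laboratory tests at every onsite visit for all patients (a reduced laboratory panel at weeks 72 and 96). The excluded data will therefore exist.

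**Step 2: what is not covered elsewhere.** Footnote o collects renal and cardiovascular composite events, arrhythmia, hospitalization, emergency dialysis, emergency visits and death, without a binder condition. For a patient without a binder, two things remain uncovered:
- AEs that are not a listed event. Examples are symptomatic hypotension, or acute kidney injury that leads to neither hospitalization nor an emergency visit.
- Descriptive safety summaries. Low potassium is one case: the normokalemia endpoints use 3.5–5.0 mmol/L, so a value below 3.5 is pooled with values above 5.0 as not normokalemic, and the severe-hyperkalemia endpoint separates only the high side.

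**Step 3: the two collection rules.**

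| | Table 1 footnote p | Assessment and data collection |
|---|---|---|
| Scope | Binder-related AEs and SAEs, plus special situations for one product | AEs and SAEs, no restriction stated |
| Start | Consent (prior users) or binder start (new users); none for never-users | Not tied to a binder |
| End of recording | "until 24 h post-discontinuation" | Tracked throughout the study |

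Scope and recording period differ.

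**Step 4: size.** The article gives no expected binder share, so the shares below are assumptions. Patients outside the safety set = 1,000 × (1 − share). For an event seen zero times in n patients, the one-sided 95% upper bound is 1 − 0.05^(1/n).

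| Assumed binder share | Safety set n | Outside | Zero-event upper bound |
|---|---|---|---|
| 30% | 300 | 700 | 0.99% |
| 50% | 500 | 500 | 0.60% |
| 70% | 700 | 300 | 0.43% |
| 90% | 900 | 100 | 0.33% |
| All enrolled | 1,000 | 0 | 0.30% |

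The last column shows scale only. The binder-treated and all-enrolled sets are different populations, so the main loss is of representation rather than precision.

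**The case against.** The strongest reply is that the harms most relevant to RAASi optimization are already covered. Severe hyperkalemia, arrhythmia, renal and cardiac composites, eGFR slope and acute care are secondary endpoints. They fall under the FAS by default, and footnote o gathers the clinical events from everyone. Subgroups by RAASi use and hyperkalemia treatment pattern are also planned for the primary and selected secondary endpoints. All of this stands. A reader might infer that patients without a binder receive no safety evaluation, or that the schedule gathers nothing but binder-related events. The article supports neither inference.

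Two further inferences also go too far. The 24-hour limit in footnote p might seem to clash with following AEs to the end-of-study visit. It does not: the first limits when events are collected, and the second governs follow-up of events already recorded. And if *related* in footnote p means causally attributed, AE and ADR counts would largely coincide, but the exposure-based window also allows an on-treatment reading, so that consequence is not established.

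It can fairly be added that a binder-exposed set suits product safety reporting, that footnote p routes AEs of other companies' products to the respective authorization holders, and that the study is descriptive and single-arm, so causal safety claims are limited anyway. These points explain why a binder set exists. They do not explain why it should be the only population for laboratory, ECG, vital-sign and physical findings, nor do they remove the disagreement on AE scope and recording period.

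**Conclusion.** The point holds in a limited form. As written, the plan omits patients without a binder from the AE/SAE/ADR counts and from the safety summaries of vital signs, physical examination, ECG and laboratory data. It also gives two incompatible descriptions of AE scope and recording period. The conclusion takes the vital-sign, examination, ECG and laboratory sentence to share the population named at the head of its paragraph, which is the natural reading.

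The number affected is unknown. Between 100 and 700 of 1,000 patients corresponds to an assumed binder share of 90% down to 30%, and the mismatch exists at any share below 100%. The primary endpoint and its precision are untouched. It would be too strong to conclude that the trial can say nothing about the safety of RAASi optimization, because the FAS endpoints speak to its main potassium, renal and cardiac harms.

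**What to change.** 1. Summarise laboratory values (including potassium below 3.5 mmol/L), ECG, vital signs and physical findings in all enrolled patients who entered the management period.
2. Keep the binder-exposed set for binder-attributed AEs and ADRs, counted over footnote p's window: from consent for prior users and from initiation for new users. Counting from first binder dose would put the start before consent for prior users.
3. Reconcile footnote p with Assessment and data collection so that one AE scope and one recording period apply. Say whether *related* means causally attributed or occurring on treatment. If the narrow scope is kept, state that AE conclusions apply to binder-exposed patients only.

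Items 1 and 2 need changed wording and a few extra tables from data already scheduled in Table 1. Item 3 adds site reporting only if the wider scope is chosen. Timing favours settling item 3 first. Trial status expected the last enrollment by January 24, 2026, which puts week 48 at about December 26, 2026 (336 days later) and week 96 at about November 27, 2027 (672 days later). The tables can still be changed before the primary analysis, but AEs left unrecorded meanwhile may not be recoverable.
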